### Study aims

The Study of Novel Approaches to Weight Gain Prevention (SNAP) is a two site, randomized clinical trial funded by the National Heart Lung and Blood Institute. The two clinical sites are at The Miriam Hospital ([name], PI) and The University of North Carolina at Chapel Hill ([name], PI). The Coordinating Center is at Wake Forest School of Medicine ([name], PI). SNAP is comparing the efficacy of self-regulation plus small behavior changes intervention, a self-regulation plus large behavior changes intervention, and a minimal treatment control condition in preventing weight gain in 600 young adults age 18 – 35 over an average planned follow-up of 3 years.

The primary hypothesis is that the magnitude of weight gain across 3 years will differ among the three groups. Specific *a priori* hypotheses are that the magnitude of weight gain across the 3 years will be lowest in the self-regulation plus large behavior changes intervention, followed by the self-regulation plus small behavior changes intervention, and greatest in the control condition.

Secondary aims compare the 3 conditions on mean weight gain at 2 years, on the proportion who gain <1 pound or >1 pound at 3 years, and on the proportion who become obese at 3 years. The three groups are also compared on changes in behavior (e.g. diet, physical activity, disordered eating behaviors, use of healthy and unhealthy weight control practices), psychosocial measures (restraint, depression), and changes in CVD risk factors (including blood pressure, lipids, insulin sensitivity, and waist circumference). The study will also examine demographic and psychological variables that may predict weight change over the average follow-up of 3 years and/or moderate the effects of the interventions, including initial BMI, ethnicity, age, scores on the Eating Inventory, and treatment preference and examine potential mediators of the effect of the interventions, including changes in diet, physical activity, restraint, self efficacy and frequency of self-weighing.

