## Methods

### Study design

SNAP targets the enrollment of 600 participants, who are randomly assigned with equal probability to 1 of 3 treatment groups, stratified by clinical center:

1. Self-guided behavior changes (Control)

2. Self-Regulation Plus Small Behavior Changes

3. Self-Regulation Plus Large Behavior Changes

Assessments are completed at baseline, 4, 12, 24, 36 and 48 months. Since enrollment is staggered, all participants are scheduled to complete the 24-month follow-up, 80% are scheduled to complete 36 months and 20% are scheduled to complete the 48-month assessments. The study was approved by the Institutional Review Boards at Lifespan-The Miriam Hospital, The University of North Carolina at Chapel Hill and Wake Forest University Health Sciences.

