### Sample size calculation

The targeted sample size (N=600 total; N=200/arm) is projected to provide ≥ 90% statistical power to detect an average pairwise difference of 3.0 lbs (1.36 kg) weight change over time between intervention arms, while accommodating anticipated rates of lost follow-up (an accumulating 7.5% at Month 4, an additional 7.5% at Month 12, and 5%/year thereafter). Comparisons of this primary outcome will be based on generalized linear models for longitudinal data. The targeted sample size provides 90% power to detect a relative 28% reduction in the proportion of participants who gain weight over time, an important secondary outcome, based on generalized estimating equations.

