### Analysis plan

The primary outcome measure, changes in weight from baseline over time, is assessed at 4-, 12-, 24-, 36- (80% of cohort), and 48-months (20% of cohort). All measured weights will be included in the analyses, except any that may have occurred during a pregnancy or within 6 months post-partum. Weight changes will be contrasted among intervention groups using generalized linear models fitted by maximum likelihood with an unstructured covariance matrix [42], with clinic site included as a covariate. Estimated mean differences for each pairwise comparison will be developed using linear contrasts and assessed with Wald statistics, using Bonferroni adjustment to control total Type I error to be 0.05 across the three comparisons.

In the primary analysis, missing weight measurements will be assumed missing at random, but additional analyses will be conducted related to missing data (e.g. comparing baseline characteristics of completers vs non-completers and creating propensity scores). If missing data appear to have the potential of influencing interpretations, we will also conduct multiple imputations using several different models for non-ignorable missingness. These will be used to assess the range of impact that missing data may exert on our results. To gauge the sensitivity of our results to any changes in height, we will conduct supporting analyses of changes in BMI.

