The secondary aims will be examined as follows. Pairwise differences in the secondary outcome measure, weight gain of greater than 1 pound from baseline (yes/no), will be assessed using generalized estimating equation (GEE) methods. Pairwise differences in mean weight changes from baseline to 24 months post-randomization among intervention arms will be assessed with linear contrasts and Wald tests within the framework of the general linear models used for the primary aim. Two-sided tests will be used with Bonferroni-adjustment to maintain overall Type I error for this secondary aim at 0.05. Generalized linear models will be used to compare the changes in behaviors and risk factors over time among the three treatments in a manner similar to that used for assessing weight changes. The effects of demographic and psychological measures on the outcomes will be examined by including initial BMI, ethnicity, age, scores on the eating inventory, and intervention preference. Significant interaction effects will be plotted to illustrate the moderating effects, further assisting the interpretation for whom and under what circumstances the intervention has different effects. To examine potential mediators of the effect of intervention, i.e., whether or not there is evidence that changes in diet, physical activity, restraint, and self-regulatory behaviors may be in the causal pathway between the intervention and weight gain, a series of three linear regression models will be fitted to test for mediators following the procedures introduced by Baron and Kenny [43]. The Sobel’s test will be used to test the significance of the indirect effect. The joint effects of multiple mediators will also be tested [44]. For the secondary outcome of weight gain (yes/no), logistic regression models will be fitted to assess meditational effects [45].

We pre-specify three planned subgroup comparisons. We will assess, using tests of interaction, whether the relative efficacy of the intervention varies according to baseline BMI (<25 kg/m^2^ versus ≥25 kg/m^2^), age (<25 years versus ≥25 years), and gender.

The fidelity of intervention delivery within the two clinical sites will be assessed by comparing measures of adherence and weight control. Adverse events will be tallied by intervention assignment and for important clinical subgroups. We will report event rates per person years and use Poisson regression to compare rates of any commonly occurring events among intervention groups.

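### Single-step Bonferroni over the three pairwise contrasts is valid but more conservative than three arms require; Shaffer or Holm step-down gains power at the same 0.05 familywise error

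*Protocol article*

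**What the plan says.** The Study aims section gives a three-group hypothesis: "The primary hypothesis is that the magnitude of weight gain across 3 years will differ among the three groups". It then adds a predicted order, with Large Changes gaining least, Small Changes next and Control most.

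The Analysis plan names pairwise Wald tests of linear contrasts only, and sets their multiplicity rule as follows: "using Bonferroni adjustment to control total Type I error to be 0.05 across the three comparisons". With three comparisons that is 0.05/3 = 0.0167 each. For mean weight change at 24 months it says: "Two-sided tests will be used with Bonferroni-adjustment to maintain overall Type I error for this secondary aim at 0.05". Neither place describes a step-down or closed procedure.

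The Sample size calculation claims power of at least 90% with 200 per arm. The target is "to detect an average pairwise difference of 3.0 lbs (1.36 kg) weight change over time between intervention arms". It gives neither the standard deviation nor the significance level behind the 90%. Allocation to the three arms is equal.

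**The concern.** Three pairwise equalities among three means are logically linked. If A differs from B, then A = C and B = C cannot both hold. So after one correct rejection at most one true null is left, and the remaining contrasts can each be tested at 0.05 without raising the familywise error above 0.05. Single-step Bonferroni ignores this link and holds every contrast at 0.0167 throughout.

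What is at stake is power for the contrasts that the ordered hypothesis depends on. To confirm the full ordering, the trial must separate Large from Small Changes and Small Changes from Control, which are the narrower gaps. The Background says that no earlier trial has compared the small- and large-change approaches, so Large versus Small is a question particular to this trial.

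**Working it through.** **Inputs from the protocol.** 200 per arm with equal allocation; a 3.0 lb (1.36 kg) pairwise difference; power of at least 90%; total Type I error 0.05 over three comparisons. **Assumptions.** Two-sided primary tests (the protocol says two-sided only for the 24-month aim), normal arm means with equal and known variance, and a level for the 90% figure, taken both ways below.

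**The plan's own figure.** It cannot be reproduced without the SD, only solved backwards: SD = 1.36 × √(n/2) / (z for the level + z for the power).
- At 0.0167 with n = 200: 1.36 × 10 / (2.394 + 1.282) = 3.70 kg.
- At 0.05 with n = 200: 1.36 × 10 / (1.960 + 1.282) = 4.20 kg.
- With 150 analysable per arm: 3.20 kg and 3.63 kg.

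The stated power is attainable but not confirmed. The comparison of procedures needs only the standard error that the 90% implies.

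**Reading A: the 90% was set at 0.0167.** The pairwise standard error is 3.0/3.676 = 0.816 lb. Bonferroni power for a 1.5 lb gap is Φ(1.5/0.816 − 2.394) = Φ(−0.556) = 29%. Simulation (1,000,000 draws of three arm means) gives, per contrast:

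| True means (lb) | Contrast | Bonferroni | Holm | Shaffer |
|---|---|---|---|---|
| 0/-3/-3 | each active v control | 90% | 92% | 94% |
| 0/-3/-6 | adjacent | 90% | 96% | 96% |
| 0/-1.5/-3 | adjacent | 29% | 37% | 44% |

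At 0/-3/-6 lb, power to establish all three differences rises from 80% to 91%.

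**Reading B: the 90% was set at an unadjusted 0.05.** Bonferroni per-pair power for 3.0 lb is Φ(3.242 − 2.394) = Φ(0.848) = 80%. Shaffer gives 87% at 0/-3/-3 lb and 90% per adjacent contrast at 0/-3/-6 lb. Full closure (a 2-df test at 0.05, then each pair at 0.05) gives 88% and 90%.

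**Familywise error.** With all arms equal: 0.044 for Bonferroni, Holm and Shaffer alike, since their first step is the same. With exactly two arms equal: 0.017 for Bonferroni (0.05/3), 0.042 for Holm and 0.050 for Shaffer in the 0/-3/-3 lb case. None exceeds 0.05.

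**Size in participants.** For Bonferroni to match Shaffer's power under reading A, the sample size per arm must be multiplied by ((2.394 + z for the new power)/3.676)². For 94.2% power this is (3.964/3.676)² = 1.16. For 95.7% it is (4.109/3.676)² = 1.25. That is 16-25% more analysable participants per arm.

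**Interval mismatch.** A contrast that Shaffer rejects and Bonferroni does not has |z| between 1.960 and 2.394, so its Bonferroni interval covers zero. Under reading A, at least one such contrast appears in about 11% of trials at 0/-3/-3 and 0/-3/-6 lb, and in 29-30% when adjacent gaps are 1.5 to 2 lb.

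**Adding a 2-df test.** As a test of three-group equality, its power against that of at least one significant Bonferroni pair is 97.4% v 96.7% at 0/-3/-3 lb and 91.9% v 91.1% at 0/-1.5/-3 lb.

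**The case against.** The strongest reply is that nothing here is wrong. Bonferroni is pre-specified, valid, covers all three contrasts, and gives simultaneous intervals that agree with the tests. That agreement is a legitimate reason to prefer it, and the mismatch under a step-down procedure is not trivial. All of this stands, and it limits the point to efficiency.

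A reader might infer that the primary hypothesis is never tested, because no 2-df test is named. The documents do not support that. Any Bonferroni-significant pair is itself a valid 0.05-level rejection of three-group equality, and the 2-df test would add less than one percentage point. The pairwise contrasts also address the ordered hypotheses more directly than an omnibus test would. An analysis plan that is not shown may contain one.

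A reader might also infer that a 2-df test at 0.05 followed by pairwise tests at 0.05 always rejects at least as often as Bonferroni. It does so on average, but not in every dataset. Bonferroni needs z² above 5.73, and the 2-df gate needs 5.99. With the middle arm exactly halfway, the 2-df statistic equals z² for the extreme contrast, so a z between 2.394 and 2.448 passes Bonferroni and fails the gate. This happens in up to 0.27% of simulated trials. Shaffer and Holm never lose a Bonferroni rejection.

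Finally, the 29% to 44% gain uses gaps of half the design difference. At the design difference of 3.0 lb the gain under reading A is 4 to 6 points.

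**Conclusion.** The point holds as a cheap improvement. The stated rule is valid but stricter than needed for both the primary and the 24-month comparisons. At the 3.0 lb design difference, Shaffer adds about 4 to 6 points of per-contrast power if the sample was sized at 0.0167, and about 6 to 10 points if it was sized at an unadjusted 0.05. The gain is larger where adjacent arms are closer together. The absolute powers rest on the assumed sizing level, two-sided tests and a normal approximation. The direction does not depend on the missing SD, because a step-down procedure cannot reject less than Bonferroni. The documents do not support reading this as a flaw in error control or as a failure to address the primary hypothesis.

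**What to change.** In the Analysis plan, replace single-step Bonferroni with Shaffer's step-down for both the primary and the 24-month comparisons: test the contrast with the smallest p-value at 0.0167 and, if it is rejected, test each of the other two at 0.05. Holm (0.0167, 0.025, 0.05) is an acceptable, slightly weaker alternative. A 2-df Wald test of equal arm means may be reported alongside as the direct test of the three-group hypothesis, but it should not be a gate that is claimed to dominate Bonferroni.

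State which intervals will be shown. If they are Bonferroni simultaneous intervals, say that they do not correspond to the step-down tests and that a significant contrast may have an interval covering zero.

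The cost is a sentence or two and that loss of agreement; no participants or data are needed. Because the article describes a trial in progress whose monitoring board reviews weight outcomes, the change should be dated and fixed before any unblinded comparison. If agreement between tests and intervals is valued more than the extra power, keeping Bonferroni is defensible, and the plan should give that reason.

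### The >1 lb weight-gain outcome is assigned to GEE with no missing-at-random handling tied to it, although the same weights are analysed under missing at random in the primary model and losses of 20-25% are planned

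*Protocol article*

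**What the plan says.** All statements are in the protocol article.

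- **Primary outcome (Analysis plan).** Weight changes are compared with "generalized linear models fitted by maximum likelihood with an unstructured covariance matrix". On missing values: "In the primary analysis, missing weight measurements will be assumed missing at random".
- **Binary secondary outcome (Analysis plan).** "weight gain of greater than 1 pound from baseline (yes/no), will be assessed using generalized estimating equation (GEE) methods". No working correlation, weighting, imputation or missing-data assumption is given for it. The 24-month mean change, by contrast, is kept inside the primary model. The Sample size section calls the binary outcome important and bases its power on GEE.
- **Planned loss (Sample size calculation).** "an accumulating 7.5% at Month 4, an additional 7.5% at Month 12, and 5%/year thereafter".
- **Further missing-data work (Analysis plan).** The examples are "comparing baseline characteristics of completers vs non-completers and creating propensity scores". Then: "If missing data appear to have the potential of influencing interpretations, we will also conduct multiple imputations", and these are to use models for non-ignorable missingness. The text neither extends this work to the binary outcome nor limits it to the primary one.

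**The concern.** The yes/no outcome is a cut of the weights that the primary model uses. A likelihood model uses each person's earlier weights to account for a later missing one. GEE on the observed yes/no values makes that adjustment only indirectly, through the working correlation. If people who have gained by one visit tend to miss the next, the proportion who gained is understated among those still seen.

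A between-arm contrast is at risk mainly if the mechanism differs by arm. The design leaves room for that. The active arms receive monthly zone feedback, and quarterly calls go to people above starting weight or not reporting; controls get one session and web newsletters. Whether this raises or lowers retention of gainers is not known. At stake is whether the mean-weight result and the binary result could diverge through their missing-data assumptions alone.

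**Working it through.** **1. Planned loss.** Adding the stated losses: month 4, 7.5%; month 12, 7.5 + 7.5 = 15%; month 24, 15 + 5 = 20%; month 36, 20 + 5 = 25%. Compounding instead: 1 - 0.925 x 0.925 x 0.95 = 18.7% at month 24 and 1 - 0.925 x 0.925 x 0.95 x 0.95 = 22.8% at month 36. The additive reading is used below (92.5/85/80/75% retained). Only 80% of the cohort is scheduled for month 36, but that follows from entry date and is not dropout.

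The 90% power stated for this outcome comes without a control proportion or within-person correlation. It can be neither confirmed nor refuted and is not used here.

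**2. Assumed inputs (none is in the protocol).** Months 4/12/24/36:
- Mean change: Control +0.3/0.9/1.8/2.7 kg; Large -2.3/-1.5/-0.4/+0.6 kg.
- SD 2.5/3.5/4.5/5.2 kg, normal. Correlations: 0.70, 0.55, 0.45 (month 4 with 12, 24, 36); 0.75, 0.65 (month 12 with 24, 36); 0.80 (month 24 with 36).
- Month-4 loss unrelated to weight. Later dropout has log-odds rising by 0.3 per kg of change at the last visit seen, with the intercept set to the planned retention.

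True month-36 proportions above 1 lb (0.45 kg):
- Control: Φ((2.7 - 0.45)/5.2) = Φ(0.43) = 66.7%.
- Large: Φ((0.6 - 0.45)/5.2) = Φ(0.03) = 51.1%.
- Ratio 51.1/66.7 = 0.77; difference -15.6 points.

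**3. What GEE returns at month 36.** With arm-by-visit means and an independence working correlation, GEE returns the observed proportions. Runs of 200,000 to 400,000 per arm gave about 62.9% in Control and 46.5% in Large where the mechanism acted. The same data were refitted with an exchangeable working correlation.

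| Dropout linked to gain in | Independence: Control / Large | Ratio | Error in difference, independence | Error in difference, exchangeable |
|---|---|---|---|---|
| neither arm | 66.7 / 51.1 | 0.77 | 0 | 0 |
| Large only | 66.7 / 46.5 | 0.70 | -4.6 points | -1.1 |
| Control only | 62.9 / 51.1 | 0.81 | +3.8 | +0.7 |
| both | 62.9 / 46.5 | 0.74 | -0.8 | -0.3 |
| opposite (gainers leave Control, losers leave Large) | 63.0 / 56.0 | 0.89 | about +8.5 | +2.8 |

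The control-only ratio was 0.81 to 0.82 depending on the intermediate correlations.

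**4. Weaker mechanism.** At 0.1 per kg the independence ratio is 0.74 (Large only), 0.79 (Control only) and 0.76 (both). The exchangeable difference is then off by 0.3 to 0.4 points.

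**5. A second set of assumptions.** Control +0.2/0.8/1.6/2.4 kg; intervention -1.2/-0.8/0/+0.8 kg; SD 3/4/5/5.5 kg; correlation exp(-0.2 x years apart); slope 0.8 per SD.
- Independence differences, true to observed: Control only -0.116 to -0.083; intervention only -0.112 to -0.150; both -0.115 to -0.118; opposite -0.122 to -0.046.
- Exchangeable: -0.124, -0.113, -0.115 and -0.111, all within about 1 point of the truth. These came from 8,000 per arm, so simulation error is itself about √(2 x 0.25/6,000) = 0.009.

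**The case against.** **The protocol does not say the GEE is unweighted.** A reader might infer an ordinary, unweighted analysis. The wording also covers weighted GEE or GEE after imputation, and the propensity scores mentioned in the Analysis plan could feed such weights. This is a condensed article, and detail for a secondary outcome may sit in an analysis plan that is not shown. This stands: there is no contradiction and no wrong figure. What remains is that the article names the estimator for this outcome and ties missing at random only to the primary analysis. The only imputation that it names is conditional and aimed at non-ignorable loss.

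**GEE does not require loss completely at random.** A reader might infer that it does. It also tolerates dropout that depends on arm, visit and modelled covariates. This stands.

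**The larger distortions come from one specification.** In the one-arm cases the relative reduction of about 0.23 shifts by 0.05 to 0.07, that is, by 20-30%. A reader might take that as the expected error. It arises only with an independence working correlation, and an exchangeable one removes most of it. This stands, but the article names no working correlation, so the protection cannot be assumed.

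**Gain-related dropout is not documented.** The retention section names pregnancy as the largest source of loss in earlier studies. Assessment visits get top priority, tracing contacts are held, and follow-up visits are paid. This stands: the mechanism is plausible but assumed.

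**Conclusion.** The point holds as a mismatch of assumptions with an inexpensive remedy. The same weights are protected under missing at random in one analysis and not assuredly in the other, with 20-25% loss planned by months 24-36.

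Under the assumed trajectories and a slope of 0.3 per kg, independence GEE understates an affected arm's 36-month proportion by about 4-5 points. It moves the ratio from 0.77 to between 0.70 and 0.82 when one arm is affected. A shared mechanism gives 0.74 and changes the difference by under 1 point. Exchangeable GEE is off by about 1 point or less in these cases and about 3 points if the mechanisms are opposite. All sizes rest on assumed means, SDs, correlations and slopes; a slope of 0.1 gives much less.

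Severity is low to moderate. A reader might infer that the primary result is also in doubt; the documents do not support that, since the primary model is likelihood-based under the assumption it states.

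**What to change.** State the missing-data assumption for the >1 lb outcome and align it with the primary analysis, in one of two ways:

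1. Multiply impute the continuous weights separately by arm under missing at random, using earlier and later weights, site, gender, ethnicity and baseline weight. Leave the pregnancy and post-partum exclusions as planned. Dichotomise each completed set at >1 lb, fit the GEE and combine the results.
2. Fit a GEE weighted by the inverse probability of remaining observed, given earlier weight change.

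The working correlation should be named in either case. The non-ignorable imputations already foreseen can be built on the same imputed weights.

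The cost is programming time and slightly wider intervals. Option 1 also relies on the imputation model describing weights near the 1 lb cut reasonably well. No change to data collection, sample size or the primary analysis is needed.

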#### Psychological measures

**Eating disorders assessment (EDA)** Participants complete a questionnaire used in Look AHEAD that assesses the frequency of binge eating episodes accompanied by loss of control, and the frequency of compensatory behaviors including vomiting, diuretics, and fasting. These data are used to exclude individuals with bulimia nervosa at baseline and identify any individuals who meet criteria for this eating disorder during the trial.

**Eating inventory** The Eating Inventory (TFEQ) [33] is a 51-item self-report instrument with three factors, assessing dietary restraint, disinhibition and hunger. The Restraint factor (range 0–21) assesses the degree of conscious control one is exerting over eating behaviors; the Disinhibition factor (range 0–16) measures susceptibility to loss of control over eating; and the hunger factor (range from 0–14) assesses hunger.

**Autonomous motivation** Autonomous motivation for preventing weight gain is measured with the Treatment Self Regulation Questionnaire [34,35]. Half of the items reflect autonomous motivation (e.g. “Because I feel that I want to take responsibility for my own health”) and half reflect controlled motivation (e.g. “Because I would feel guilty or ashamed of myself if I did not try to control my weight”).

**Depression** The Center for Epidemiologic Studies Depression Scale (CES-D) [36], a self-report depression scale designed to measure depression symptoms in the general population is administered at baseline and each assessment visit.

**Life events** The life events questionnaire from the Coronary Artery Risk Development in Young (CARDIA) study lists 67 events and participants are asked to indicate whether or not that event has occurred since the last visit [37]. We have chosen to use the CARDIA life events questionnaire in preference to other similar questionnaires (e.g. Holmes and Rahe) [38] because it was developed specifically for young adults and reflects the type of life events that occur most commonly in this age group.

**Perceived stress** The Cohen Perceived Stress Scale [39] is a 4-item self-report instrument that captures the participant’s perception of stress in their lives over the past month. The Perceived Stress Scale poses general questions about current stress levels.

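### Moderator plots and the for-whom interpretation are tied to statistical significance, in a trial sized only for a main effect

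*Protocol article*

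**What the plan says.** The Study aims section of the protocol article lists, after the primary and secondary comparisons, an examination of "demographic and psychological variables that may predict weight change over the average follow-up of 3 years and/or moderate the effects of the interventions".

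The Analysis plan takes this up. The effects of these measures on the outcomes "will be examined by including initial BMI, ethnicity, age, scores on the eating inventory, and intervention preference". The next sentence is the one at issue: "Significant interaction effects will be plotted to illustrate the moderating effects, further assisting the interpretation for whom and under what circumstances" the intervention works differently.

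A separate paragraph, after the mediation text, begins "We pre-specify three planned subgroup comparisons". It will assess, "using tests of interaction, whether the relative efficacy of the intervention varies according to baseline BMI", age and gender, with BMI and age each cut at 25. That paragraph attaches no significance condition to what is shown.

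The only power statements concern main effects. For mean weight, the trial is to have at least 90% power "to detect an average pairwise difference of 3.0 lbs (1.36 kg) weight change over time" between arms, with 200 participants per arm. No power is stated for any interaction. Bonferroni adjustment is stated for the three primary contrasts and for the 24-month mean change. The article mentions none for the moderator tests, but a multiplicity rule for them may sit in the analysis plan that is not shown, so its absence is not the point here.

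**The concern.** An effect shown because it passed a significance test is, on average, larger than the true effect, and the lower the power, the larger the excess. The sentence picks the moderator effects to be plotted by significance and then uses the plots to say who benefits. The trial is sized for an average difference between arms. An interaction is estimated with at least twice the standard error of that difference, so this is where selection distorts most.

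The practical stake is the for-whom message. The trial compares two competing approaches to weight gain prevention, and the Discussion names translation into community or commercial use as the next step if either succeeds. A plot that overstates, say, a BMI or treatment-preference interaction could influence who is offered which approach. The primary conclusion is not affected.

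**Working it through.** **Inputs.** From the Sample size calculation: difference 3.0 lb = 1.36 kg, power at least 90%, 200 per arm, loss 7.5% + 7.5% + 5% per year. From the Analysis plan: primary alpha 0.05/3 = 0.0167 per contrast; five named moderators. From Psychological measures: the Eating Inventory "is a 51-item self-report instrument with three factors, assessing dietary restraint, disinhibition and hunger", so five moderators become seven if its scores are tested separately. From Eligibility: recruitment goals of at least 25% men and 25% from racial/ethnic minority groups, which motivate a 25/75 split as well as 50/50. Assumed, because the article does not say: interaction tests two-sided at 0.05, one independent test per moderator, a binary moderator, equal variances.

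**The plan's own figure.** The unit conversion is right (3.0 × 0.4536 = 1.36). The 90% cannot be confirmed or refuted, because no SD or correlation is given. At a single time point it would need an SD of 4.20 kg (alpha 0.05, 200 per arm) down to 3.20 kg (alpha 0.0167, 75% retained, 150 per arm). The SD is not needed below: anchoring on the stated power fixes the standard error directly.

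**Standard error of a main contrast.** SE = 1.36 / (z for alpha + z for power).
- Alpha 0.05: 1.36 / (1.960 + 1.282) = 0.420 kg
- Alpha 0.0167: 1.36 / (2.394 + 1.282) = 0.370 kg

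**Standard error of an interaction.** With subgroup share f, the multiplier is √(1/(f(1−f))): 2.00 at f = 0.50 and 2.31 at f = 0.25.
- f = 0.50: 0.74–0.84 kg; smallest estimate reaching p < 0.05 is 1.96 × SE = 1.45–1.64 kg
- f = 0.25: 0.85–0.97 kg; smallest such estimate 1.67–1.90 kg

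**Power and overstatement.** Let μ = true interaction / SE. Power = 1 − Φ(1.96 − μ) + Φ(−1.96 − μ). Overstatement = mean of |z| among draws with |z| > 1.96, divided by μ (2,000,000 simulated draws per case). Example for f = 0.50, main alpha 0.05 and a true interaction of 1.36 kg: μ = 1.36/0.839 = 1.62, power = 0.37, overstatement 1.63. Over both alphas and both splits:

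| True interaction | Power | Overstatement when significant |
|---|---|---|
| 2.72 kg (twice the main effect) | 80–96% | 1.03–1.12× |
| 1.36 kg (equal to it) | 29–45% | 1.5–1.8× |
| 0.68 kg (half) | 11–15% | 2.7–3.5× |
| 0.34 kg (a quarter) | 6–8% | 5.2–6.8×, wrong sign in 10–16% |

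**Chance findings.** If no moderator is real, P(at least one significant) = 1 − 0.95^k: 1 − 0.95^5 = 0.23 and 1 − 0.95^7 = 0.30.

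**Share of significant results that are false.** With π the share of moderators that are real, this is 0.05(1 − π) / [0.05(1 − π) + π × power]. At power 0.12–0.15 it is 57–63% for π = 0.2 and 25–29% for π = 0.5. At power 0.40 and π = 0.3 it is 23%. The article gives no basis for choosing π.

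**The case against.** The strongest reply is that the sentence describes how a detected interaction will be illustrated, in a secondary aim worded tentatively, in an article that condenses a fuller document. Table formats, alpha and multiplicity for moderators normally go in the analysis plan. Much of this stands, and it rules out several stronger readings that a reader might infer:

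- *That non-significant interactions will be withheld.* The text does not say so. It sets a condition for plotting, not for reporting.
- *That the three pre-specified subgroups are filtered too.* They are in their own paragraph, with fixed cutpoints for BMI and age, tested by interaction, and no filter is stated. That is sound practice.
- *That most plotted interactions would be false.* This needs an assumed share of real moderators, and the answer changes over a plausible range, as shown in the working.
- *That any significant interaction must exceed the whole design effect.* The plan says at least 90%. At 95% power and alpha 0.0167 the main SE is 1.36/(2.394 + 1.645) = 0.337 kg, and the 50/50 threshold is 1.96 × 0.674 = 1.32 kg, just below 1.36 kg.
- *That each moderator is tested by three unadjusted pairwise contrasts*, which would raise the chance-finding rate. The article never states this.

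It is also fair that BMI, age and the Eating Inventory scores are naturally continuous, so no single kilogram threshold applies to them, and that the three Eating Inventory scores may not be independent. The binary figures are an illustration.

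What the reply does not remove is the rule itself. The sentence makes significance the criterion for display and links that display to a statement about who benefits. That choice is written in the article, not left to another document.

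**Conclusion.** The point holds as a minor one. The plan ties moderator plots, and the for-whom reading drawn from them, to statistical significance, although the trial is sized only for a 1.36 kg pairwise main effect. Interactions up to about that size are underpowered and would be materially overstated when selected this way; for interactions of twice that size the distortion is negligible.

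The power and overstatement figures rest on exactly 90% main-effect power, interaction tests at 0.05 and a binary moderator with a 25–50% share; higher main-effect power would soften them. The 23% and 30% also assume one independent test per moderator and no true interaction. None of this supports a statement about how many significant moderators would be false, or a criticism of the three pre-specified subgroup tests.

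**What to change.** Replace the sentence on plotting significant interactions with:

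> For each named moderator (initial BMI, ethnicity, age, Eating Inventory scores, intervention preference) the interaction estimate with its 95% CI will be reported and displayed whatever its p-value; these analyses are exploratory, and statistical significance alone will not support a for-whom conclusion.

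Showing every listed interaction removes the selection, so the displayed set is no longer inflated by it, and the intervals let readers see how imprecise each estimate is. If the full protocol or analysis plan already provides this, aligning the article's wording is enough. A formal multiplicity adjustment is not needed for this purpose.

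The cost is one complete table or figure in place of selected plots. No new data, visits or sample size are involved. The only thing given up is the freedom to make a for-whom statement from a single significant interaction.
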